#### Randomization

The unit of randomization will be the participant and the randomization process will use computer generation of group assignment with a 1:1 allocation ratio. Participants will be stratified by site (three YMCA sites) and by walking ability (10-m walk speed ≤ 0.9 m/s [household or limited community ambulator] or > 0.9 m/s [unlimited community ambulator]) [55]. We will block the randomization with variable block size unknown to the sites. Once participant consent has been obtained and baseline assessment completed, the LRC will enter the Methods Centre at McMaster University to report the participant characteristics needed for stratification into REDCap, a secure web-based data management system, and receive the group allocation, thus ensuring concealment of randomization.

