#### Intervention group: FIT for FUNCTION

The 12-week FIT for FUNCTION program comprises an exercise component (2×/week group classes, 1×/week independent exercise) and a self-management / education component (1×/week).Exercise: group exercise sessions (60 min, 2×/week) will be delivered by a kinesiologist trained to work with individuals with stroke. A stroke rehabilitation physiotherapist will provide on-site consultation 4 h per week and remote consultation 3 h per week. These group classes were adapted from the Community-Based Exercise Program for Persons Living with Stroke [56] and a DVD training package was developed for staff as a standardized competency-based approach. The exercise classes comprise: (i) warm up (10 min); (ii) task-oriented strengthening and cardiovascular conditioning (20 min); (iii) mobility and balance (20 min); and (iv) cool down (10 min). The feasibility of this program was established in the pilot study, with no adverse events and four participants (6.6%) withdrawing from the program (one related to the intervention and three unrelated to the intervention). From the pilot study, we found that maintaining a class size of 12 and a staff:participant ratio of 1:4 was important for ensuring safety of all participants. See Additional file 4 for a detailed description of the exercise program.

Of note, the cardiovascular conditioning component will be enhanced in this proposed trial. Individualized prescriptions will be determined using HR reserve and rating of perceived exertion methods that we have used extensively in previous stroke trials [37, 39]. Participants will also attend an independent exercise session (1×/week), where they will have full access to equipment and facilities at the YMCA.

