To assess the effect of the intervention on RNLI (research question 1), physical activity levels, physical functioning, QOL, cardiovascular health, and self-management (research question 2), we will estimate group, time, and group × time interaction effects using generalized linear models for continuous variables. We will include relevant baseline variables as covariates in the analysis that differ between groups at baseline, notably time since stroke (TSS) if there is a significant between-group difference. We will also include the baseline score for the specific measure of interest. For example, for research question 1, the baseline score of the RNLI would be included as a covariate for evaluating post-program changes.Our hypothesis is that there will be reduced hospitalizations and physician visits for the intervention group compared to the control group (research question 3). Cost data are usually treated as non-parametric; therefore, a Mann–Whitney U test will be used to test relative ranks of participants between the groups on relative intervention cost.We will use prognostic indicators from participants’ profiles to determine factors associated with the greater benefit from the FIT for FUNCTION program (research question 4). These factors will be identified by expanding the models for the treatment effects on RNLI and function as the dependent variables, and using prognostic variables of co-morbidities, illness severity, depressive symptoms, mobility impairment and cognitive status, education, previous level of activity, stroke classification, and interactions involving age and gender, as independent variables in the regression models.

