A limitation of the trial, as with most rehabilitation trials, is that it is not possible to blind the participants. Therefore, participants who are randomized to the control group may find it more difficult to adhere to exercise where there is less standardization and support compared to the intervention group. In addition, expanding this intervention to other YMCAs that have their own institutional idiosyncrasies may result in some site-specific effects, so we plan to examine the results of the trial by site. A further consideration is how time since stroke may influence the primary outcome of reintegration and may introduce bias. Persons who have low reintegration scores at one year, for example, may be different from participants with stroke who have low scores at 30–60 days which would result in the population at risk being different at the assessment time points. Persons who enter the trial at shorter time post stroke may have more spontaneous improvement and reintegrate earlier biasing the comparison to the null while persons who enter later may have more severe disease which will decrease the likelihood of a response in either group. To address this issue, we will adjust for time since stroke in our analyses and also use time since stroke to create subgroups to examine the outcomes.

A novel aspect of this study is it will be the first community-based trial to examine exercise-associated changes to cardiovascular risk factors. Despite the known increase in risk for recurrent events [4], cardiovascular risk factors are often poorly managed after stroke [13, 66]. The benefits of fitness training on walking ability are clearly established [102] but there is insufficient evidence that analogous improvements in cardiovascular risk factors can be observed. Few studies have included risk factors as outcomes and most have been conducted in research settings or in other controlled environments with smaller sample sizes. This study offers a large sample size to contribute to the state of the evidence related to changes in these risk factors following exercise and is the first community exercise trial to inform how to implement such strategies for secondary prevention within a sustainable community program model.

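### Only the FIT for FUNCTION arm is treated in shared classes, yet the stated model and sample size make no allowance for within-class correlation and the model omits the stratification factors; the net error rate is not established

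*Protocol article*

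**What the plan says.** The protocol article's Randomization section fixes individual allocation: "The unit of randomization will be the participant and the randomization process will use computer generation of group assignment with a 1:1 allocation ratio". It then states: "Participants will be stratified by site (three YMCA sites) and by walking ability".

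Treatment differs in structure between the arms. In the section on the intervention group, "group exercise sessions (60 min, 2×/week) will be delivered by a kinesiologist trained to work with individuals with stroke", and the pilot is reported to have shown that "maintaining a class size of 12 and a staff:participant ratio of 1:4 was important for ensuring safety of all participants". The same arm attends a weekly group education course of eight sessions. Under Control group, controls come as often as they choose and may use eight coaching sessions with YMCA staff who are not involved in the programme. Under Contamination, staff who deal with the intervention group have no contact with controls.

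For the analysis, the Analyses section states: "we will estimate group, time, and group × time interaction effects using generalized linear models for continuous variables". On covariates it adds baseline variables that differ between the groups, notably time since stroke, and: "We will also include the baseline score for the specific measure of interest". Table 2 lists the same model family for RNLI and the other clinical outcomes. The Sample size justification uses a t-test on change scores with no design effect. The Discussion expects some site-specific effects: "so we plan to examine the results of the trial by site".

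**The concern.** People who exercise together twice a week and share an education group have an instructor, peers and a season in common. The primary outcome is reintegration into social life, so some similarity within a class is plausible. If it exists, the mean of the FIT arm varies more than the same number of independent people would, while the control mean does not. A model that treats all participants as independent then gives too small a standard error for the group effect on RNLI and on every other outcome analysed the same way.

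The listed model also leaves out the factors used to stratify randomisation. Because stratification balances site and walking speed by design, the rule of adding covariates that differ at baseline is unlikely to bring them in. Leaving out strata that predict the outcome makes the standard error too large. The two omissions act in opposite directions, and the plan gives no means of knowing which dominates.

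**Working it through.** **The plan's own sample size.** Inputs from Sample size justification: difference 3.1, SD 3.23, two-sided alpha 0.05, 80% power. n per group = 2 × (1.960 + 0.842)² × (3.23/3.1)² = 17.04, so 18 (19 with the t distribution), not the printed 105. The 105 is reproduced with an SD of about 8.0. The chosen 91 per group at a difference of 3 implies an SD of √(91 × 3² / (2 × 2.802²)) = 7.22, which is used below for power. That mismatch is a separate matter. What counts here is that none of these figures contains an allowance for clustering.

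**Effect of clustering in one arm.** Assumptions: 108 per arm, independent controls, equal total variance in the arms, and a model that is otherwise correct. The class size m = 12 is the pilot figure. The ICC is assumed.

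- Design effect in the FIT arm: DE = 1 + (m − 1) × ICC
- Variance ratio for the difference: V = (DE + 1)/2
- True two-sided error of a nominal 5% test: 2 × [1 − Φ(1.96/√V)]

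| ICC | DE | V | True SE / reported SE | Type I error | Simulated (9 × 12 vs 108) | Coverage of 95% CI | Power, 91 per group, SD 7.22 |
|---|---|---|---|---|---|---|---|
| 0 | 1.00 | 1.000 | 1.00 | 5.0% | 5.0% | 95.0% | 80% |
| 0.01 | 1.11 | 1.055 | 1.03 | 5.6% | 5.7% | 94.4% | 78% |
| 0.02 | 1.22 | 1.110 | 1.05 | 6.3% | 6.5% | 93.7% | 76% |
| 0.05 | 1.55 | 1.275 | 1.13 | 8.3% | 8.1% | 91.7% | 70% |
| 0.10 | 2.10 | 1.550 | 1.24 | 11.5% | 11.7% | 88.5% | 61% |

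The simulation used 40,000 trials per row. In it, a class-level variance for the FIT arm with Satterthwaite degrees of freedom brought the error back to 5.0% to 5.4%. If the one-sided 0.05 level in the footnote to Table 2 applied instead, the five error rates would be 5.0%, 5.5%, 5.9%, 7.3% and 9.3%.

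**Smaller clusters.** Trial status gives recruitment from October 2014 to December 2017, about 39 months or 169 weeks, which is about 14 periods of 12 weeks. The FIT arm has 108/3 = 36 people per site. At even accrual that is 36/14.1, or about 2.5 new FIT participants per site per 12 weeks. With m = 3, V = 1.02, 1.05 and 1.10 at ICC 0.02, 0.05 and 0.10, and the error is 5.2%, 5.6% and 6.2%.

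**Effect of omitting the strata.** Let the strata explain a share R² of outcome variance, and take the ICC as a share of what remains. Then approximately V = (1 − R²) × (DE + 1)/2. For R² = 0.10 and m = 12, V = 0.900, 0.999 and 1.148 at ICC 0, 0.02 and 0.05, so the error is 3.9%, 5.0% and 6.7%. A simulation with three sites and two walking strata (6,000 trials per case) gave 3.9%, 5.1% and 6.7%. For R² = 0.20 it gave 2.9%, 3.7% and 5.0%. Once the strata were in the model, the error was about 6% at ICC 0.02 and about 8% at ICC 0.05. R² is also an assumption; the documents do not give it.

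**The case against.** The strongest case on the other side is that the size of the problem is conditional throughout. The documents give no ICC. Twelve is the pilot class size. Nothing says whether classes are fixed cohorts or take new members continuously, and even accrual points to far fewer than 12 trial participants starting together at one site. The omitted strata pull the error down and can offset a moderate ICC. All of this stands, and it limits the point. Two qualifications apply. Adjustment for baseline RNLI would probably absorb part of what the strata explain and so shrink the offset. And relying on one omission to cancel another is not a sound basis for a primary test.

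It can also be said that random effects and degrees of freedom belong in an analysis plan that is not shown, and that the sample size text speaks of controlling for function. This stands in part: such a plan could supply the missing terms. But the article does name the model terms and bases its sample size on independent participants, and neither makes room for class or site.

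A reader might go further and infer three things that the documents do not support:

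- That the false-positive rate of the plan exceeds 5% as a matter of fact. That needs a positive ICC that outweighs the missing strata.
- That the error favours the programme. A standard error that is too small widens both tails alike and does not shift the estimate.
- That the plan for site effects is defective for want of a treatment × site term. The Discussion already plans to look at results by site, and that wording does not exclude an interaction test.

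Nor do the documents say that controls exercise alone or that each site has its own kinesiologist.

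**Conclusion.** The concern holds in conditional form. Clustering arises in one arm only, and the stated model and the sample size both ignore it; the model also omits the stratification factors. If outcomes correlate within class and the model is otherwise correct, two-sided error is about 5.6% to 11.5% for classes of 12 with ICC 0.01 to 0.10, and about 5.2% to 6.2% for clusters of about 3 with ICC 0.02 to 0.10. With no correlation it is 5.0%. Omitting the strata moves it the other way by an unknown amount, so no net error rate can be assigned to the plan as written. The omission itself is certain; its size rests on the assumed ICC, cluster size and share of variance explained by the strata.

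**What to change.** Change the model wording for RNLI and the other continuous outcomes in three respects:

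- Include site and walking-speed stratum as fixed effects.
- Record a class or cohort identifier for every FIT participant. Attendance is already recorded, but the protocol does not say that the record identifies the class, so this should be stated. If entry to classes is rolling, define the cluster by site and calendar period of class attendance.
- Fit a partially nested mixed model: a random class effect in the FIT arm only, arm-specific residual variance and small-sample degrees of freedom.

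The cost is one data item, revised wording and somewhat wider intervals. With nine classes, the Satterthwaite degrees of freedom are (DE + 1)² / (DE²/8 + 1/107), or about 30, 25, 21 and 17 at ICC 0, 0.02, 0.05 and 0.10. The t multipliers are about 2.04, 2.06, 2.08 and 2.11. Multiplying each by √V and dividing by 1.96 gives intervals about 4%, 11%, 20% and 34% wider than those of the independence analysis. Where the ICC is positive, most of that widening is the uncertainty that the independence analysis leaves out. Adding the strata should recover some precision if they predict the outcome.

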**Methods/Design:**

This single-blinded, randomized controlled trial (RCT) of 216 participants with stroke will compare the effectiveness of a 12-week YMCA community-based wellness program (FIT for FUNCTION) specifically designed for community-dwelling persons with stroke to persons who receive a standard YMCA membership. The primary outcome will be community reintegration using the Reintegration to Normal Living Index at 12 and 24 weeks. Secondary outcomes include measurement of physical activity level using the Rapid Assessment of Physical Activity and accelerometry; balance using the Berg Balance Scale; lower extremity function using the Short Physical Performance Battery; exercise capacity using the 6-min walk test; grip strength and isometric knee extension strength using hand held dynamometry; and health-related quality of life using the European Quality of Life 5-Dimension Questionnaire. We are also assessing cardiovascular health and lipids; glucose and inflammatory markers will be collected following 12-h fast for total cholesterol, insulin, glucose, and glycated hemoglobin. Self-efficacy for physical activity will be assessed with a single question and self-efficacy for managing chronic disease will be assessed using the Stanford 6-item Scale. The Patient Activation Measure will be used to assess the patient’s level of knowledge, skill, and confidence for self-management. Healthcare utilization and costs will be evaluated. Group, time, and group × time interaction effects will be estimated using generalized linear models for continuous variables, including relevant baseline variables as covariates in the analysis that differ appreciably between groups at baseline. Cost data will be treated as non-parametric and analyzed using a Mann–Whitney U test.

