#### Conceptual framework

We have used the International Classification of Functioning, Disability and Health (ICF) [49] as our conceptual framework to identify key factors associated with participation in community-based physical activity (see Additional file 3). The first component of the ICF (Impairments) will be used as covariates in analyses of research questions 1 and 2 [50]. The second component of the ICF (Activities and Participation) will be defined using relevant mobility, self-care measures, and participation measures. The concepts of our primary outcome measure, the Reintegration to Normal Living Index, have been mapped to the ICF [51]. Qualitative analyses will identify the environmental (e.g. services, systems, and policies) and personal factors (e.g. self-efficacy for physical activity) within the ICF framework that impact activities and participation.

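### Covariates other than the outcome's baseline score enter the model only if the groups happen to differ at baseline, and this conflicts with the Discussion's unconditional adjustment for time since stroke

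*Protocol article*

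**What the plan says.** The Analyses section describes one model family for research questions 1 and 2, so the rule covers the primary outcome (the Reintegration to Normal Living Index, RNLI) and the secondary outcomes. Its terms are group, time and group by time, plus covariates of two kinds:

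- Fixed: "We will also include the baseline score for the specific measure of interest".
- Conditional: "We will include relevant baseline variables as covariates in the analysis that differ between groups at baseline", and for one variable in particular, "notably time since stroke (TSS) if there is a significant between-group difference".

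The Methods/Design paragraph of the Abstract repeats the conditional rule with a different trigger and no threshold: "including relevant baseline variables as covariates in the analysis that differ appreciably between groups at baseline".

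Three other places bear on the same model:

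- Discussion: "we will adjust for time since stroke in our analyses". No condition is attached.
- Conceptual framework: "The first component of the ICF (Impairments) will be used as covariates in analyses of research questions 1 and 2". No condition is attached, and the impairments are not listed there.
- Randomization: "Participants will be stratified by site (three YMCA sites) and by walking ability". Neither factor is named among the model terms in the Analyses section. The Discussion plans to look at results by site, which is not a term in the primary model.

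**The concern.** With concealed, computer-generated allocation, any baseline difference between the arms is a chance event. Testing for it tells us nothing about whether the variable predicts RNLI, and that is the only sound reason to adjust. A strongly prognostic variable that happens to be balanced is left out, and a useless one that happens to be unbalanced is put in. The primary model cannot be written down before the data are seen, and two analysts could defend different models, because one trigger is a significant difference, another an appreciable one, and a third simply a difference.

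The conflict over time since stroke matters most. The Discussion argues on prognostic grounds: early entrants may recover spontaneously and late entrants may have more severe disease. It offers adjustment as the remedy. The Analyses section would apply that remedy only by accident.

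**Working it through.** The plan gives no figure on this point, so there is none to reproduce. The check has four parts.

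**1. How often would time since stroke enter?** The article sets no level for the baseline test; I assume the trial's 0.05. Under randomisation the test is then significant in about 5% of trials. A simulation with 216 participants, 1:1 allocation in six strata and blocks of 4 or 6 gave 4.7% to 5.2%. The adjustment promised in the Discussion would be absent in about 95% of trials.

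**2. How often would some variable be picked up by chance?** For k independent baseline tests at 0.05 the chance of at least one is 1 − 0.95^k: 23% for k = 5, 34% for k = 8, 40% for k = 10. The article does not say how many variables are screened, so k is an assumption.

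**3. What does conditional entry of time since stroke cost?** The same simulation used a linear model with the baseline score, an assumed baseline-outcome correlation of 0.5 and an assumed effect of 0.33 SD. The correlations of time since stroke and of the strata with the outcome were varied, also by assumption. A correlation r corresponds to r²/(1 − 0.5²) of the variance left after the baseline score: 0.01/0.75 = 1.3% for r = 0.1 and 0.09/0.75 = 12% for r = 0.3.

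| Correlations (strata, time since stroke) | Power, time since stroke only if significant | Power, time since stroke always | Power, time since stroke and strata always |
|---|---|---|---|
| 0.1, 0.1 | 0.79 | 0.80 | 0.80 |
| 0.3, 0.3 | 0.82 | 0.86 | 0.89 |
| 0.5, 0.3 | 0.84 | 0.89 | 0.96 |

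For type I error, a separate simulation with simple 1:1 randomisation (216 participants, 20,000 null runs) let time since stroke explain 5, 10 or 20% of the variance. Leaving it out gave 0.048, 0.049 and 0.050. Adjusting only if significant gave 0.047, 0.045 and 0.044. The conditional rule is therefore slightly conservative, not inflated.

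**4. What does including the stratification factors gain?** Let R² be the share of residual RNLI variance explained by site and walking-speed stratum (assumed 5, 10 or 20%). Because randomisation balances them, the true standard error of the treatment difference is √(1 − R²) times the one an unadjusted model reports. Take a trial that would have power 0.80 if no such factor were balanced or adjusted, so the standardised effect is 1.96 + 0.84 = 2.80.

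- Unadjusted type I error: 2 × [1 − Φ(1.96/√(1 − R²))]
- Unadjusted power: Φ(0.84/√(1 − R²))
- Adjusted power: Φ(2.80/√(1 − R²) − 1.96)

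| R² | Unadjusted type I error | Unadjusted power | Adjusted power |
|---|---|---|---|
| 0.05 | 0.044 | 0.81 | 0.82 |
| 0.10 | 0.039 | 0.81 | 0.84 |
| 0.20 | 0.028 | 0.83 | 0.88 |

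The gain is about 1 to 5 percentage points. The type I figures apply only to factors balanced by stratification. Time since stroke was not stratified, and part 3 shows that leaving it out keeps the error at its nominal level.

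**The case against.** The strongest reply is that this is a condensed article and a fuller analysis plan may settle the covariates. That holds for anything the article leaves unsaid, but here it states a rule, and states it differently in different places.

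Several stronger readings are tempting, and the documents do not support them:

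- *That every covariate is chosen by a significance test.* Significance is attached only to time since stroke. Other variables must be relevant and differ, or differ appreciably. The outcome's baseline score, often the most useful covariate, is always included.
- *That the rule inflates false positives.* The calculations point the other way: nominal or slightly conservative.
- *That the article sets out three mutually exclusive covariate rules.* The flat contradiction concerns time since stroke alone. The impairment covariates could be added to the terms in the Analyses section. They are unreconciled with it rather than opposed to it: that section names mobility impairment and cognitive status only for research question 4.
- *That the stratification factors are wrongly excluded.* No passage excludes them, and silence in an article is not an error. It remains true that a rule admitting only variables that differ will tend to pass over factors balanced by design.
- *That the trial has no power to spare.* The documents do not show this. The printed inputs in Sample size justification (difference 3.1, SD 3.23, 105 per group) give power above 99.9%. Whether those inputs are right is a separate question.

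**Conclusion.** The point stands in two parts that need no assumed figure: the stated rule selects covariates by chance imbalance, and it contradicts the Discussion on time since stroke. The impairment covariates are a third loose end. The consequence is a primary model not fixed in advance and, mainly, lost precision. The size of that loss depends on how strongly the variables predict RNLI, which the documents do not give. It is negligible at a correlation of 0.1 (power 0.79 against 0.80 with time since stroke and strata fixed) and moderate at 0.3 (0.82 against 0.89). It does not threaten the trial's validity, but it should be corrected because the remedy costs almost nothing.

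**What to change.** Delete the imbalance-driven rule from the Abstract and the Analyses section. Prespecify one covariate set for the primary and secondary models, used whatever imbalance is observed:

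- the baseline score of the outcome;
- time since stroke, on a scale stated in advance;
- site (three levels) and walking-speed stratum (at or below 0.9 m/s, or above), as used in randomisation.

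State which impairments from the Conceptual framework, if any, belong to this set, by name and measure. Then align the Abstract, Conceptual framework, Analyses and Discussion. Any adjustment prompted by observed imbalance can stay as a labelled sensitivity analysis.

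The cost is wording. Site and walking speed are needed to randomise, and time since stroke is already planned for use in the analysis. The additional terms use about four degrees of freedom (time since stroke 1 if entered as one linear term, site 2, walking stratum 1) in a trial of 216, plus any for named impairments.
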